## Abstract

Background: Heart Failure (HF) is a common chronic disease that has a high readmission rate and is associated with worsening symptoms and major financial impacts. Disease management implemented during or after an HF hospitalization has been shown to reduce hospitalization and mortality rates. Particularly for outpatients, it is necessary to provide self-care interventions. Structured nurse-led support such as timely follow-ups, including phone calls, is beneficial for improving self-care assessments. Evidence for nurse-led support has been investigated but is less than conclusive. The aim of this study is to compare the effectiveness of a nurse-led structured intervention for outpatients with chronic HF against the usual medical care in terms of self-care behaviors and occurrence of symptom exacerbation or rehospitalization. Methods and analysis: This is a cluster-randomized controlled trial. A total of 40 facilities with certified HF nurses will be allocated to two-arm clusters at a 1:1 ratio, randomly to the intervention or usual care arms. A total of 210 participants will be assigned from the hospital. Participants will be adults aged 18 years or older diagnosed with chronic HF who are classified as Stage C according to the ACCF/AHA Heart Failure staging system. In the intervention group, patients will receive structured nursing support. This begins with weekly support, including phone calls, for the first month, then transitions to monthly support thereafter. The aim is to ensure the stability of their living conditions, promote medication adherence, and encourage self-management. In the control group, patients will receive the usual care. Primary outcomes will assess the improvement or continuation of self-care behavior as measured by changes in EHFScBS (European Heart Failure Self-Care Behavior Scale) scores. Secondary outcomes include occurrence of readmission within 30 days, 3 months, 6 months, and 1 year after discharge, duration of home care until readmission, and blood levels of BNP and NT-proBNP.

## 1. Introduction

### Rationale

Heart failure (HF) is a prevalent cause of mortality worldwide and presents a considerable financial burden through repeated hospitalization expenses. This issue is a global problem. As many guidelines recommend, despite the recent advancements in drug therapy for HF, it is crucial to acknowledge the complementary role of non-pharmacological interventions in order to optimize patient outcomes [1,2]. Among non-pharmacological interventions, self-care interventions is crucial for maintaining physical and emotional stability, promoting overall health, and reducing the burden on healthcare systems, as highlighted by the European Society of Cardiology guidelines [3]. Evidence has shown that self-care interventions are particularly beneficial, as they can reduce hospitalization and mortality rates, improve quality of life, and increase knowledge about the condition.

Despite the importance of self-care interventions, there is still no consensus on the optimal approach for promoting and enhancing self-care among individuals with HF. One promising strategy is a multidisciplinary HF disease-management program that includes structured support such as timely follow-ups, including phone calls, which have been shown to be effective in improving outcomes [4]. Previous systematic reviews have demonstrated that structured telephone support has reduced all-cause mortality and HF-related hospitalizations [5,6]. Based on these results, the 2013 ACCF/AHA HF clinical practice guideline and 2019 ACC Expert Consensus Decision Pathway have described follow-up phone calls have been recommended within 72 h after admission to improve outcomes [7,8]. The Heart Failure Association of the European Society of Cardiology and some Asian cardiac societies also suggest that phone calls can theoretically assess patient symptoms, improve adherence, and lead to timely treatment. However, structured self-care interventions, including early follow-up phone calls within 72 h, require significant additional human resources and costs, resulting in limited usage of these interventions [9,10]. Despite the theoretical potential for effectiveness, research is lacking, particularly regarding the additive effectiveness of early structured telephone support [11,12]. Therefore, the effectiveness of additional early structured telephone support interventions should be re-evaluated.

Among these multidisciplinary team members, nurses are integral members, because nurse-led self-care interventions have been considered effective and cost-effective to improve cardiovascular disease, and offer numerous benefits, including a favorable perception of nurses as trusted healthcare professionals, a high quality of care delivery provided by these experts, a more frequent and consistent follow-up provided to patients, and the potential for lower healthcare expenditures [13,14]. Implementation of structured self-care interventions including early telephone support, especially by nurses, could effectively improve self-care behavior and prevent symptom deterioration among HF patients. Additionally, the intervention promotes early medical attention and shows preventive effects against worsening symptoms during unscheduled visits.

The aim of the study described in this protocol is to conduct a cluster RCT to compare the clinical effectiveness of early nurse-led structured telephone support intervention with the usual care. In addition to assessing cardiovascular outcomes, such as all-cause death and HF rehospitalization, the study will also evaluate the effectiveness of the interventions through self-care assessments, considering the mechanism of the intervention. Overall, this study could provide valuable evidence on the effectiveness of nurse-led telephone interventions in improving self-care behavior and outcomes for HF patients.

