### 2.2. Trial Design

We will conduct a cluster randomized controlled trial across different facilities to compare the efficacy of outpatient support by telephone and in person, as provided by a nurse.

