## 4. Interventions

The intervention will be conducted in healthcare facilities that provide inpatient and outpatient care for chronic HF. The intervention will be carried out by HF nurses or nurses with at least 3 years of experience in HF nursing. The intervention period is set for three months after discharge, with a focus on the first month as a period of intensive support (Figure 1).

On the third day after discharge, support is provided via phone to the patient and their family to confirm their living situation, medication adherence, and self-management status related to weight and blood pressure control. If the patient was discharged to a facility, information is gathered from the facility staff and nursing consultation and guidance is provided to the patient and staff. In-person support for approximately 30 min is provided at the first outpatient visit after discharge (usually about 2 weeks later). For one month after discharge, support is provided once a week via in-person or phone methods. Following the initial month where support is provided weekly, both in-person and phone support will be offered once a month for the next three months. Depending on the patient’s condition and the judgment of the nursing staff, additional support may be provided as needed.

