Research on structured interventions focused on post-discharge telephone support for heart failure patients is limited, but the approach holds diverse potential benefits beyond self-care management, including consultation on post-discharge life issues. It is believed to be more efficient than in-person support. Inglis et al., in their Cochrane systematic review, demonstrated the effectiveness of structured telephone support in reducing all-cause mortality (RR 0.87, 95% CI 0.77 to 0.90) and heart failure-related hospitalizations (RR 0.85, 95% CI 0.77 to 0.93) [5,6]. Inouye et al. showed that automatic telephone follow-up 48 h post-discharge can identify high-risk patients for readmission among heart failure patients. Such structured interventions centered on post-discharge telephone calls are not limited to heart failure but are implemented across various domains [22]. Miller et al., through a retrospective analysis including non-heart failure cases in a single-center setting, demonstrated significantly lower readmission rates within 7 days of discharge and a trend toward lower rates within 30 days with telephone follow-up within 72 h post-discharge, which aligns with the approach adopted in this study [23]. This study aims to further evaluate the effectiveness of structured telephone interventions, with an initial call scheduled at 72 h post-discharge.

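### The protocol states two aims, early telephone support and a combined nurse programme, and its two-arm design can answer only the second

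*Protocol article*

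**What the plan says.** Telephone-specific statements in the protocol article:

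- Section 1 (Rationale) argues that "the effectiveness of additional early structured telephone support interventions should be re-evaluated". It then gives the aim as to "compare the clinical effectiveness of early nurse-led structured telephone support intervention with the usual care" and expects that "this study could provide valuable evidence on the effectiveness of nurse-led telephone interventions" will result.
- Section 10 (Discussion) closes with: "This study aims to further evaluate the effectiveness of structured telephone interventions, with an initial call scheduled at 72 h post-discharge".

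Programme-level statements in the same article:

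- The Abstract gives the aim as to "compare the effectiveness of a nurse-led structured intervention for outpatients with chronic HF against the usual medical care".
- Section 2.2 (Trial Design) says the trial will "compare the efficacy of outpatient support by telephone and in person, as provided by a nurse".
- Section 2.6 (Study Participants) describes the intervention as a support programme with in-person and telephone parts.
- Section 10 opens by naming structured nurse-led intervention as the object of the trial, with early calls as a highlighted part of it.

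The schedule is in section 4 (Interventions). A telephone contact takes place on day 3. "In-person support for approximately 30 min is provided at the first outpatient visit after discharge", usually about two weeks after discharge. "For one month after discharge, support is provided once a week via in-person or phone methods". After that, both modes are offered monthly, and nurses may add contacts at their discretion. Section 5 (Control) gives controls routine outpatient care and withholds structured nurse support after discharge, even where a site could provide it.

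**The concern.** A reader who takes the aim from the Introduction or the end of the Discussion expects the trial to show whether early structured telephone support works. The randomised arms differ in structured in-person sessions, telephone contacts and total structured nurse contact, all at once. A benefit could come from the in-person sessions, from the calls, or from the two together. A null result would not show that early calls fail.

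This affects what may be claimed at the end. Section 9 (Ethics Approval and Dissemination) says the data will serve as evidence for policy recommendations, with revision of medical fees among the examples. A result reported under the telephone-specific aim could be cited for or against telephone follow-up as such, which the comparison does not test.

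**Working it through.** The plan gives no figure to reproduce here. The check has three steps.

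**1. What differs between the arms** (sections 4 and 5, Abstract)

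| Element after discharge | Intervention | Control |
|---|---|---|
| Day-3 call | required | no |
| In-person nurse session, about 30 min, first outpatient visit | required | no structured session |
| Weekly contacts, month 1 | either mode | no |
| Monthly contacts afterwards | both modes | no |
| Extra contacts | nurse's judgement | no structured support |
| Routine outpatient visits | yes | yes |

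There are two arms, allocated 1:1. The randomised contrast is therefore:

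effect estimated = mean outcome under (calls + in-person sessions + extra contacts) − mean outcome under usual care.

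A telephone effect added to other support would be:

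mean outcome under (calls + in-person sessions) − mean outcome under (in-person sessions alone).

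The second term of that difference has no arm. The same holds for the 72 h call taken alone.

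**2. How much of month 1 must be by telephone** (section 4 and the Figure 1 legend)

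Assumptions: four weeks to the month, the first outpatient visit counts as one weekly contact, and no extra contacts are made.

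- *Reading A: the day-3 call is the first weekly contact.* Total = 4. Fixed: 1 call and 1 in-person session. Free: 4 − 2 = 2. Calls run from 1 + 0 = 1 to 1 + 2 = 3, so the telephone share is 1/4 = 25% to 3/4 = 75%.
- *Reading B: the day-3 call is additional to four weekly contacts.* The Figure 1 legend supports this, since it places the weekly contacts after the call. Total = 5. Fixed: 1 call and 1 in-person session. Free: 5 − 2 = 3. Calls run from 1 + 0 = 1 to 1 + 3 = 4, so the share is 1/5 = 20% to 4/5 = 80%.

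On both readings the smallest number of calls that complies with the schedule is one, and at least one contact is in person. These are limits on permitted schedules. They are not estimates of what will be delivered, nor of the share of any effect due to calls.

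**3. Whether recorded data could separate the modes** (section 6)

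The dates, times and numbers of telephone and in-person sessions are recorded in the intervention arm. However, the mode of the flexible weekly contacts is not randomised, and extra contacts depend on the patient's condition and the nurse's judgement. A comparison of patients by number or share of calls would therefore be observational and open to confounding by severity. It cannot stand in for a randomised telephone contrast.

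**The case against.** The strongest reply is that the article, read as a whole, tests a package in which the early call is a prominent element, and that the telephone wording is shorthand. The Abstract, sections 2.2 and 2.6 and the opening of the Discussion support this. Even the Introduction, just before its aim, speaks of structured self-care support that includes early calls. Comparing a package with usual care is a normal pragmatic design, and the Statistical Method section promises no analysis by component.

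Much of this stands. It shows that the telephone-specific aim is one of two in the article, and it makes the remedy a matter of wording. It does not remove the problem, because the formal aim sentence of the Introduction, its expected conclusion and the closing aim of the Discussion remain telephone-specific, and the design cannot deliver them.

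Four stronger readings are tempting, and the document supports none of them:

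- *That the randomised comparison is invalid.* It is valid for the programme as a whole.
- *That the cost of early calls is the reason for the trial.* The Rationale attaches the staffing and cost burden to structured self-care interventions, of which early calls are a part, and uses it to explain their limited use. The reason it gives for the trial is lack of research.
- *That intervention patients will typically get one call in month 1.* One is the minimum, not the expected number.
- *That controls have no in-person contact.* They have routine visits, and section 6 records any face-to-face guidance they receive. What they lack is structured nurse support after discharge.

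**Conclusion.** The concern holds as an inconsistency of aim. The article states a telephone-specific aim and a programme-level aim, and the two-arm design answers only the latter. The comparison of the combined programme with usual care stands, and nothing here bears on the sample size or the arms. A conclusion about structured telephone support, or about the 72 h call, does not follow from this contrast, whatever mix of modes is delivered, because an in-person session is required in the intervention arm.

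The month-1 range (1 to 3 calls of 4 contacts, or 1 to 4 of 5) rests on the assumptions given with the count. It illustrates how loosely the telephone share is fixed; the conclusion does not depend on it.

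The correction should be made because it changes what the trial may claim, and the results are intended for policy use.

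**What to change.** - In section 1 (Rationale), reword the aim and the expected conclusion to the effect of a combined in-person and telephone nurse support programme compared with usual care. Reword the closing aim in section 10 in the same way. Both then agree with section 2.2.
- State once, in the objective or the limitations, that the separate effect of the telephone component or of the 72 h call cannot be estimated from this design.
- Using data that section 6 already collects, report the number and share of telephone and in-person sessions in the intervention arm, and the face-to-face guidance given to controls. Label this as description, not as evidence for either component.

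The cost is a few sentences and one descriptive table. The arms, sample size, schedule and clinical care do not change. The downside is a less specific claim.

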## 2. Methods and Analysis

### 2.1. Trial Registration

The trial is registered with the Japan registry of clinical trials (ID:1030220447). Trial registration was completed before participant recruitment. Modifications to the protocol will be updated online.

### 2.2. Trial Design

We will conduct a cluster randomized controlled trial across different facilities to compare the efficacy of outpatient support by telephone and in person, as provided by a nurse.

### 2.3. Sample Size

A sample size of 210 (105 in each arm) will allow us to detect a difference of four units in the EHFScBS scores with 80% statistical power. Assumptions are based upon data from the CHART-2 study, which estimated a mean clinical estimated difference of 4 in the EHFScBS before and after intervention, with a standard deviation of 8.5 [15,16]. The ICC was 0.05, and a dropout rate of 30% due to mortality or other reasons over one year was assumed, based on previous research results, in order to determine the sample size [17,18].

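### The 80% power stated for 210 patients does not follow from the sample-size inputs printed beside it; with 40 facilities they give about 74–76%

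*Protocol article*

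**What the plan says.** Section 2.3 of the protocol article gives the size and the target together: "A sample size of 210 (105 in each arm) will allow us to detect a difference of four units in the EHFScBS scores". The power claimed for this is 80%. The effect is taken from an earlier cohort study and described as a "mean clinical estimated difference of 4 in the EHFScBS before and after intervention"; the SD is given as 8.5. The allowances are in the next sentence: "The ICC was 0.05, and a dropout rate of 30% due to mortality or other reasons over one year was assumed". The section presents these figures as the basis on which the sample size was fixed.

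The number of clusters is in the Abstract: "A total of 40 facilities with certified HF nurses will be allocated to two-arm clusters at a 1:1 ratio". Section 8 compares the arms on change from discharge to 1 and 3 months. The article states no alpha, sidedness, assumed cluster size or design effect.

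**The concern.** All the inputs needed to check the 80% are printed, except alpha. Before any allowance for clustering, a 4-unit difference with SD 8.5 needs about 71 evaluable patients per arm. The plan's own dropout takes 105 down to 73.5. That leaves a margin of fewer than three patients per arm for clustering, too little for an ICC of 0.05 across 40 facilities.

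Power for the primary outcome is a stated property of the design, and readers will judge a null result by it. If the figure does not follow from its inputs, either the figure or an input needs changing. The same paragraph also calls the 4 units a before-after difference, while the trial tests a difference between arms.

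**Working it through.** **Inputs**
- Difference 4, SD 8.5, ICC 0.05, dropout 30%, 105 per arm, power 80%: Section 2.3.
- 40 facilities, 1:1, so 20 per arm: Abstract.
- Two-sided alpha 5%: assumed, because the article gives none.
- Equal facility sizes: assumed.

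**Reproducing the printed 105 per arm**
1. Unclustered size: n = 2(1.960 + 0.8416)² × 8.5² / 4² = 70.9 per arm.
2. Patients analysed per facility: 210 × 0.7 / 40 = 3.675.
3. Design effect: 1 + (3.675 − 1) × 0.05 = 1.134.
4. Evaluable patients needed at that cluster size: 70.9 × 1.134 = 80.4 per arm.
5. Allowance for 30% loss:
   - dividing by 0.7: 80.4 / 0.7 = 114.8 per arm, or 230 in total;
   - multiplying by 1.3: 80.4 × 1.3 = 104.5, which rounds up to 105 per arm, or 210 in total.

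The second route matches the printed figure. Leaving clustering out gives 70.9 / 0.7 = 101.3, or 102 per arm and 204 in total, which is close but not equal. Multiplying by 1.3 does not compensate for a 30% loss, because 105 × 0.7 = 73.5, short of the 80.4 needed.

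**Power at 210 under the stated inputs**
1. Effective size: 73.5 / 1.134 = 64.8 per arm.
2. Standard error of the difference: 8.5 × √(2/64.8) = 1.493.
3. Standardised difference: 4 / 1.493 = 2.679.
4. Normal approximation: Φ(2.679 − 1.960) = 76.4%.
5. Noncentral t with 40 − 2 = 38 degrees of freedom (critical value 2.024): 74.2%.

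**Detectable difference at 80% power, 210 patients**
- Normal: (1.960 + 0.8416) × 1.493 = 4.18 units.
- t, 38 df: 4.29 units.

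**Total needed for 80% power with 40 facilities and 30% loss**

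The cluster size grows with enrolment, so the 230 above is slightly too low: at 230 the analysed cluster size is 4.025 and power is 79.5% (normal). Solving with the cluster size tied to the total gives the following.

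| Reference | Total | Power at that total |
|---|---|---|
| Normal | 234 | 80.0% |
| t, 38 df | 250 | 80.1% |

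**Loss at which 210 still gives 80% power** (cluster size recalculated each time)

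| Loss | Normal | t, 38 df |
|---|---|---|
| 30% | 76.4% | 74.2% |
| 22% | 80.0% | 78.0% |
| 17% | 82.0% | 80.0% |
| 16% | 82.3% | 80.4% |

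**The case against.** The strongest reply concerns the dropout. The 30% is a one-year figure, whereas the self-care comparison is at 1 and 3 months. If loss accrued at a constant rate (an assumption, for illustration only), 30% in a year would be 1 − 0.7^(1/4) = 8.5% at 3 months, and power at 210 would be 84.8% (normal) or 83.0% (t, 38 df). This stands to the extent that the shortfall is conditional on the printed dropout. It does not rescue Section 2.3, which gives 30% as the design assumption and no 3-month figure.

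Three other replies carry less weight.
- **Alpha is unstated.** At one-sided 5%, 210 would exceed 80% power, but the same calculation would then call for about 182 patients (194 with a cluster size of 5.25). That reading does not explain 210 either.
- **Covariate adjustment could recover power.** Section 8 allows it only where judged necessary, and it is not among the sample-size inputs.
- **The gap is modest.** It is about 4 to 6 percentage points. Unequal facility sizes, which the check ignores, would widen it.

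Two stronger readings are tempting, and the documents do not support them. A reader might infer power as low as 71%. That figure pairs the 73.5 analysed patients per arm with the enrolled cluster size of 210/40 = 5.25, and so mixes two samples. A reader might also infer a far larger loss of power, on the ground that controls receive self-monitoring education (Section 5) and may improve too. The article gives no figure for control-arm improvement, and its operative sentence takes 4 units as the difference to be detected. Any between-arm value below 4 would be the reader's own.

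**Conclusion.** The point holds as an inconsistency between printed inputs and a printed result. With two-sided 5% assumed and equal facility sizes, 210 patients give about 74–76% power for 4 units, not 80%. It is not established that the trial will have less than 80% power at 3 months, since that depends on a loss rate the article does not give. Nor can the article show how 105 was derived. Multiplying by 1.3 is the route that matches exactly, and it suggests that clustering was allowed for and the dropout allowance misapplied.

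The description of the 4 units as a before-after difference is a separate defect of wording in the same paragraph. It does not enter the 74–76%.

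**What to change.** Revise Section 2.3 in one of two ways, neither of which adds enrolment.
1. Keep the 30% dropout, and restate the power at 210 as about 74–76%, or the difference detectable at 80% power as about 4.2–4.3 units.
2. Replace the one-year 30% with a justified loss for the 3-month primary comparison. The 80% statement can stay if that loss is no more than about 22% (normal), or 16–17% (t, 38 df).

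In either case, state alpha and sidedness, the cluster size and design effect, and that the dropout allowance divides by one minus the loss. State that the 4 units is the assumed between-arm difference, and whether 8.5 is the SD of the score or of its change.

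The cost is a few sentences. Under the first option the stated power becomes slightly less favourable; under the second a source for 3-month loss is needed.

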## 5. Control

During hospitalization, the usual medical care and discharge instructions according to the patient’s condition are provided, in the same manner as for the intervention group. In the outpatient setting, routine outpatient visits and care are also provided in each medical institution. The usual care is based on the concept of self-monitoring for HF patients and follows the disease-management program outlined within the heart failure guideline in Japan. Therefore, patient education during hospitalization is conducted appropriately, specifically including providing education to HF patients on self-monitoring their symptoms and other findings. However, regarding post-discharge care, even if the environment for structured nurse interventions is available, these are not implemented in the control group, in order to ensure a clear distinction between the intervention and usual care [19].

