## 8. Statistical Method

The Japan Nursing Association will submit the data received from the intervention and control groups’ medical institutions to a contracted data analysis organization for analysis. The between-group comparison of the change in self-care behavior continuity and changes in BNP and NT-proBNP in the baseline values at discharge and changes after intervention (1 and 3 months later) will be performed. The Spearman rank correlation coefficient will be used to measure the relationship between the scores of cardiac functions and the EHFScBS. The Mann–Whitney U-test will be used to compare the scores of the EHFScBS between the two groups with respect to patient backgrounds. The McNemar test will be used to analyze the changes in the two groups’ readmission and symptom deterioration rates, with the corresponding t-test employed for frequency, relative risk, and absolute risk reduction for risk difference. The presence or absence of readmission and the time to readmission between the intervention and control groups will be analyzed by the Kaplan–Meier method and tested for significance using the log-rank test. The Cox proportional hazard model and propensity score analysis will be used to compare between-group differences. Multiple imputation techniques will be employed to handle missing data, ensuring robustness and reducing bias in the findings. In the above analysis for the comparison, covariate adjustment from the baseline patient characteristics will be applied to gain efficiency in the estimation for the treatment effect, when it is necessary.

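### The 4-unit effect behind the sample size is justified by a before-after change but used as a between-arm difference, with no control-arm change stated

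*Protocol article*

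**What the plan says.** Section 2.3 of the protocol article states that 210 patients, 105 in each arm, "will allow us to detect a difference of four units in the EHFScBS scores with 80% statistical power". It does not say whether that difference is between arms or within an arm. The effect and SD are credited to an earlier cohort study, which is said to have "estimated a mean clinical estimated difference of 4 in the EHFScBS before and after intervention, with a standard deviation of 8.5". The remaining inputs follow: "The ICC was 0.05, and a dropout rate of 30% due to mortality or other reasons over one year was assumed". The significance level is not given.

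Section 8 describes what will be compared: "The between-group comparison of the change in self-care behavior continuity and changes in BNP and NT-proBNP in the baseline values at discharge", with follow-up at 1 and 3 months. The Abstract likewise defines the primary outcome through changes in EHFScBS scores. Lower scores are better (Section 3.1), so improvement means a fall in score.

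Section 5 describes usual care. Controls receive the same inpatient care and discharge instructions as the intervention group, and "patient education during hospitalization is conducted appropriately, specifically including providing education to HF patients on self-monitoring their symptoms and other findings". After discharge they have routine outpatient visits without structured nurse support. No section states what EHFScBS change is expected in this arm.

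**The concern.** A before-after change and a between-arm difference in change are different quantities. The before-after figure holds everything that moves the score over time. The randomised contrast keeps only what differs between arms. The two coincide when controls do not change. If the intervention arm improves by 4 and controls improve by c, the contrast is 4 − c.

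Section 2.3 takes a figure of the first kind and attaches the trial's power to it as though it were of the second kind. At stake is the one power figure the protocol offers for its primary outcome. If the source's 4 includes improvement that controls would share, the trial is weaker for the effect its own source implies than a reader of Section 2.3 would believe. Section 9 says the results will serve as evidence for policy recommendations, so the stated power will matter when they are read.

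**Working it through.** **Inputs.** From Section 2.3: difference 4, SD 8.5, power 80%, ICC 0.05, dropout 30%, 105 per arm. From the Abstract: 40 facilities, so 20 per arm. Assumed: two-sided 5%, and that SD 8.5 applies to the quantity analysed.

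**Step 1: which formula gives 210?**

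Two-sample: n per arm = 2(1.96 + 0.8416)² × 8.5² / 4² = 70.9, so 71.

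- Dropout only: 71 / 0.7 = 101.4, so 102 per arm and 204 in total, within 3% of 210.
- With clustering: completers per facility = 105 × 0.7 / 20 = 3.675, and the design effect is 1 + 0.05 × (3.675 − 1) = 1.134. Then 71 × 1.134 × 1.3 = 104.6, so 105 per arm and exactly 210. Multiplying by 1.3 understates the dropout allowance; dividing by 0.7 gives 115 per arm, 230 in total.

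Paired before-after: n = (1.96 + 0.8416)² × 8.5² / 4² = 35.4, so 36 patients in a single group.

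The stated figure therefore fits a two-arm calculation with 4 entered as the between-arm difference. It does not fit a before-after calculation.

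**Step 2: power at the planned size.** Completers per arm = 105 × 0.7 = 73.5. Without clustering, SE = 8.5 × √(2/73.5) = 1.40. With the design effect, the effective number is 73.5 / 1.134 = 64.8 per arm and SE = 8.5 × √(2/64.8) = 1.49.

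Power is from the noncentral t. In the clustered column the lower figure uses 38 degrees of freedom (40 facilities minus 2) and the higher uses the effective sample size.

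| Intervention change | Assumed control improvement | Net difference | Power, no clustering | Power, ICC 0.05 and 40 facilities |
|---|---|---|---|---|
| 4 | 0 | 4 | 81% | 74–76% |
| 4 | 1 | 3 | 57% | 50–51% |
| 4 | 2 | 2 | 29% | 26% |

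A normal approximation gives clustered figures of 76%, 52% and 27%.

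**Step 3: what a null result could exclude.** The 95% half-width is about 1.96 × 1.40 = 2.7 units without clustering and 1.96 × 1.49 = 2.9 with it, or about 3.0 using t on 38 degrees of freedom. An estimate near zero would then exclude net effects above about 3 units.

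**The case against.** The strongest reply is that the power sentence is conditional: it promises 80% for a difference of 4, and Section 2.3 can be read as setting 4 as the between-arm target. The wording of the source description is also garbled and might mean a clinically chosen difference. This stands in part. The fault lies in the justification of the 4, and the two-sample arithmetic using 4 is not in dispute here. But the protocol cites the before-after figure as the support for its target, and that figure measures something else.

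A reader might infer three stronger things that the documents do not support.

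- *That 80% power holds only if controls do not change at all.* Power is also kept if controls worsen or if the intervention arm improves by more than 4. Conversely, zero control change still leaves 74–76% once the ICC and dropout are applied.
- *That controls will improve.* The education quoted from Section 5 is given in hospital, to both arms, and so largely precedes the discharge baseline. Section 2.7 does not select on EHFScBS: any one of ten issues qualifies, among them living alone. Regression to the mean in this score is therefore not shown. Control improvement is possible, but neither its presence nor its size can be read from the protocol. Drift peculiar to this trial's patients would also fall on both arms and cancel.
- *That a non-significant result could say nothing about effects below 4.* Step 3 of the working shows otherwise.

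It is also fair that the table rests on assumed control changes, that the meaning of SD 8.5 is unstated, and that the baseline adjustment allowed in Section 8 could recover some precision. A fuller derivation may sit in the full protocol, but the article does state the effect, its source and the power together, and as stated they do not match.

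**Conclusion.** The point holds as a mismatch between the evidence for the effect and the comparison it is used for. The 4 units are supported by a before-after change, entered as a between-arm difference, and not reduced for any control change.

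If 4 is the intervention arm's expected change, each unit of control improvement costs roughly 24 to 28 percentage points of power: from 81% to 57% to 29% without clustering, and from about 75% to 50% to 26% with it. This rests on a two-sided 5% level, 30% dropout, SD 8.5 for the analysed change, no gain from covariate adjustment, and control improvements of 0, 1 and 2 units, which are illustrations and not forecasts. It does not show that the trial is underpowered. It shows that the stated 80% lacks support for the contrast to be tested.

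**What to change.** In Section 2.3, keeping 210 patients:

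1. Define the target as the between-arm difference in EHFScBS change from discharge, at a named follow-up time.
2. Stop presenting the before-after 4 as that difference. State the control-arm change assumed and the reason for it.
3. Say whether SD 8.5 is of the score or of the change, and state the significance level.
4. Replace the single 80% claim with cluster-adjusted power at net differences of 4, 3 and 2 units (74–76%, 50–51% and about 26% on the assumptions above), recomputed if the SD turns out to mean something else.

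A null result should be interpreted from its confidence interval, with no advance statement of what it cannot exclude.

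The cost is a rewritten paragraph and a short recalculation, with no extra patients or facilities. The drawback is a less favourable stated power.
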